### Sample Size and Power Calculation

The sample size calculation is based on a random intercept model comparing the primary outcome (PHQ-ADS at T3) between treatment conditions while accounting for the nested structure of the data. Although this model is simpler than the target statistical analyses for the primary outcome presented below, it allows to avoid speculative assumptions about numerous unknown model parameters. The focal hypothesis is that both intervention groups PSYCHOnlineTHERAPY_fix/flex_ are not inferior to CBT_standard_ (= non-inferiority trial). Non-inferiority is assumed if the confidence interval (CI) of the standardized mean comparissson between PSYCHOnlineTHERAPY_fix/flex_ is completely above SMD = −0.24, which is considered as a lower threshold of clinical significance (49). We assume one-sided tests with α = 0.025 (Bonferroni-adjusted) and 1-ß = 0.8, an intra-cluster correlation coefficient (ICC) of 0.01 with a median cluster size of 12 eligible patients as feasible number to be recruited within the recruitment period. Based on these assumptions, the present trial aims at a sample size of 25 psychotherapy outpatient practice clusters and *n* = 300 patients per study arm with an allocation ratio of 1:1:1 (PSYCHOnlineTHERAPY_fix_, PSYCHOnlineTHERAPY_flex_, CBT_standard_; for formulas see (50).

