#### Primary Outcome

The primary outcome is depression and anxiety severity at post-treatment 18 weeks post-inclusion (T3), assessed with the Patient Health Questionnaire Anxiety and Depression Scale [PHQ-ADS; 16 items, score range: 0–48; (51)]. Depression and anxiety symptoms at all other assessments will be considered as secondary outcomes. PHQ-ADS is the combined sum score of the questionnaires Generalized Anxiety Disorder Screener (GAD-7) and Patient Health Questionnaire (PHQ-9) as a composite measure of depression and anxiety, with good internal consistency [α = 0.88–0.92; (51)].

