### Statistical Analyses

#### Clinical Analyses

The primary outcome will be analyzed using a three-level random slope model with measurement points nested in patients and patients nested in therapists. We will include data on depression and anxiety severity assessed at four measurement points, including baseline (T0), inter-session assessments at six (T1) and 12 weeks (T2) follow-up, and post-treatment at 18 weeks post-inclusion (T3). Depression and anxiety severity will be predicted from log-transformed time (i.e., weeks since baseline), dummy-coded treatment groups, and their interactions. Random intercepts and slopes will be included to account for unexplained heterogeneity in baseline status and rate of change, both at the level of patients and therapists. The focal tests of non-inferiority will be based on the bootstrap CIs of the interactions between time and groups. All statistical analyses will be performed based on intention-to-treat (ITT) principle. Patterns of missing data will be examined and analyses will be corrected for missing data by applying multiple imputation. Additional multiple PP analyses will be conducted including only patients that provided data.

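### The non-inferiority margin is a standardized T3 difference, but the focal test is on a log-time slope interaction for which no margin is stated

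*Protocol article*

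**What the plan says.** Three sections of the protocol article define the primary decision.

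- **Primary Outcome** fixes the endpoint: "The primary outcome is depression and anxiety severity at post-treatment 18 weeks post-inclusion (T3"). PHQ-ADS at every other assessment is secondary.
- **Sample Size and Power Calculation** describes a calculation "based on a random intercept model comparing the primary outcome (PHQ-ADS at T3) between treatment conditions". Non-inferiority requires that the confidence interval of the standardized mean comparison "is completely above SMD = −0.24, which is considered as a lower threshold of clinical significance". This section admits that its model is simpler than the planned analysis.
- **Clinical Analyses** specifies a three-level random slope model over T0 to T3. Severity is predicted from log-transformed weeks since baseline, group dummies and their interactions. It then states: "The focal tests of non-inferiority will be based on the bootstrap CIs of the interactions between time and groups".

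No sentence carries the margin of −0.24 over to the interaction.

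**The concern.** The first two sections make the decision quantity a standardized difference between arms at one time point. The third makes it a difference in rate of change per log-unit of time, estimated from four visits. These quantities have different units, and they give the visits different weights. The trial's one confirmatory conclusion, for each blended arm, is whether an interval clears −0.24, so it matters which quantity the interval describes. If two analysts bridged the gap differently, they could reach different non-inferiority verdicts from the same data.

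**Working it through.** **1. Which quantity the planned sample size supports.** The inputs are from Sample Size and Power Calculation: margin 0.24 SD, true difference 0, one-sided α 0.025, power 0.80, ICC 0.01, cluster size 12.

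- Before clustering: 2 × ((1.960 + 0.842)/0.24)² = 272.5 per arm.
- Design effect: 1 + (12 − 1) × 0.01 = 1.11.
- Required: 272.5 × 1.11 = 302.5, so 303 per arm against 300 stated. Power at 300 per arm is 79.7%.

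The stated 300 per arm therefore follows from the T3 standardized difference. The article gives no corresponding calculation for the interaction.

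**2. Converting the margin.** The log of week 0 is undefined without a constant c, and the article names none. I assume time is coded ln(week + c) and show three values. The log-time span from T0 to T3 is ln(18 + c) − ln(c). If the arms are equal at T0 and the group difference is linear in log-time, the T3 difference equals the interaction times the span.

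| Assumed coding | Span | Slope margin equal to −0.24 SD at T3 | T3 loss tolerated if −0.24 is applied to a standardized slope |
|---|---|---|---|
| ln(week + 1) | 2.944 | −0.24/2.944 = −0.082 | 0.24 × 2.944 = 0.71 SD |
| ln(week + 0.5) | 3.611 | −0.066 | 0.87 SD |
| ln(week + 0.1) | 5.198 | −0.046 | 1.25 SD |

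**3. Whether rescaling is enough.** With complete, balanced data at weeks 0, 6, 12 and 18, the slope difference is Σ wᵢdᵢ. Here dᵢ is the group difference at visit i and wᵢ = (xᵢ − x̄)/Σ(xⱼ − x̄)², with x the log-time. Multiplying by the span gives the T0 to T3 change implied by the slope. For ln(week + 1), the resulting weights on T0/T1/T2/T3 are −1.07/0.05/0.40/0.62.

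The examples below have no baseline difference. They are in SD units, and negative means worse than CBT_standard.

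| Group difference at T0/T1/T2/T3 | Actual T3 | Rescaled interaction | Against −0.24 |
|---|---|---|---|
| 0/−0.08/−0.16/−0.24 (even by week) | −0.24 | −0.22 | slightly lenient |
| 0/0/0/−0.30 | −0.30 | 0.62 × −0.30 = −0.19 | inside, though T3 is outside |
| 0/−0.30/−0.30/−0.20 | −0.20 | −0.26 | outside, though T3 is inside |

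For the other two codings, the second row gives −0.17 and −0.15, and the third gives −0.26 and −0.27. The direction of the misjudgement does not depend on the constant. These are true-value comparisons, without sampling error.

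**The case against.** The case for the plan is substantial in four respects.

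- **The sections can be read together.** The sample size section gives the criterion, and the analysis section gives the model that produces the estimate. The tests are only said to be based on the interaction intervals, so an analyst might rescale, standardize and compare with −0.24. This reading is possible, but the article does not state it, and it holds only under the two conditions above.
- **Technical details belong in an analysis plan.** The time constant and standardizing SD are commonly left to that document, and their absence alone is no fault. What remains is that this article names two different quantities for the same decision.
- **The interaction protects against baseline differences.** Patients are recruited after their practice has been allocated and trained, and Potential Problems and Solutions warns of baseline imbalance from randomizing therapists, there with therapist competency in mind. A deficit that is constant from T0 gives an interaction of zero, which is reasonable if it predates treatment. An unadjusted T3 difference would carry it into the verdict. This point stands and shapes the remedy.
- **Smooth courses lose little.** A deficit growing evenly by week to 0.24 SD reads as 0.22.

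A reader might infer that the interaction does not test the T3 outcome at all, or cannot be compared with the margin. That goes too far: T3 has a weight of 0.62, and the conversion is one multiplication under stated conditions. A reader might also apply −0.24 to a coefficient in raw PHQ-ADS points and conclude that the test has almost no power. The article says the comparison is standardized. The power of the slope test would also need its own standard error, which the article gives no basis for.

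**Conclusion.** The concern holds as an inconsistency in the primary decision rule. The endpoint, the margin and the 300 per arm all rest on a standardized T3 difference, while the focal test is placed on a slope difference without a margin on that scale.

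Applied directly to a standardized slope, the margin would be about three times too wide (0.71 SD under ln(week+1)). No section says this will be done, so it marks the size of the possible error rather than a forecast. Correct rescaling removes most of the discrepancy for smooth courses. For a late or early deficit the verdict can still go wrong in either direction, as the −0.19 and −0.26 examples show.

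The conversions assume a time constant that the article does not give. The examples assume complete, balanced data and equal arms at T0. The contradiction itself needs none of these assumptions. It should be settled before unblinding.

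**What to change.** Reconcile Sample Size and Power Calculation, Primary Outcome and Clinical Analyses on one decision quantity.

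**Preferred.** Test the model-estimated PHQ-ADS difference at T3 for each blended arm against CBT_standard. Adjust for baseline, either with baseline PHQ-ADS as a covariate or by constraining the arms to a common T0 mean. Enter visit as a category, or use a time form whose fit is checked. Compare the cluster-bootstrap confidence interval with 0.24 times a named SD fixed before unblinding; for an assumed SD of 8 to 12 points that is 1.9 to 2.9 points. State the sign convention, since higher PHQ-ADS scores mean more severe symptoms. Report the interaction as a secondary description of the course.

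**Alternative.** Keep the interaction as the focal test, multiply it by the stated log-time span, divide by the named SD and compare the result with −0.24. State the time coding, including the constant for week 0. Acknowledge that this equals the T3 difference only with equal arms at T0 and a group difference linear in log-time.

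The cost is a few sentences of wording and one SD fixed before unblinding. Neither option needs new data, and the preferred one keeps the quantity on which the 300 per arm was calculated.

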## Abstract

**Introduction:** Internet- and mobile-based interventions (IMIs) and their integration into routine psychotherapy (i.e., blended therapy) can offer a means of complementing psychotherapy in a flexible and resource optimized way.

**Objective:** The present study will evaluate the non-inferiority, cost-effectiveness, and safety of two versions of integrated blended psychotherapy for depression and anxiety compared to standard cognitive behavioral therapy (CBT).

**Methods:** A three-armed multicenter cluster-randomized controlled non-inferiority trial will be conducted comparing two implementations of blended psychotherapy (PSYCHOnlineTHERAPY_fix/flex_) compared to CBT. Seventy-five outpatient psychotherapists with a CBT-license will be randomized in a 1:1:1 ratio. Each of them is asked to include 12 patients on average with depressive or anxiety disorders resulting in a total sample size of *N* = 900. All patients receive up to a maximum of 16 psychotherapy sessions, either as routine CBT or alternating with Online self-help sessions (fix: 8/8; flex: 0–16). Assessments will be conducted at patient study inclusion (pre-treatment) and 6, 12, 18, and 24 weeks and 12 months post-inclusion. The primary outcome is depression and anxiety severity at 18 weeks post-inclusion (post-treatment) using the Patient Health Questionnaire Anxiety and Depression Scale. Secondary outcomes are depression and anxiety remission, treatment response, health-related quality of life, patient satisfaction, working alliance, psychotherapy adherence, and patient safety. Additionally, several potential moderators and mediators including patient characteristics and attitudes toward the interventions will be examined, complemented by ecological day-to-day digital behavior variables via passive smartphone sensing as part of an integrated smart-sensing sub-study. Data-analysis will be performed on an intention-to-treat basis with additional per-protocol analyses. In addition, cost-effectiveness and cost-utility analyses will be conducted from a societal and a public health care perspective. Additionally, qualitative interviews on acceptance, feasibility, and optimization potential will be conducted and analyzed.

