### Intervention

PSYCHOnlineTHERAPY provides the mean of combining standard psychotherapeutic care as described below (see control condition) with Internet- and mobile-based intervention modules. Based on psychotherapy practice study arm allocation patients receive either PSYCHOnlineTHERAPY_fix/flex_ or CBT_standard_.

All patients with a diagnosed depressive or anxiety disorder as defined in the inclusion criteria can take part in a psychotherapy reimbursed based on the PNP contract. In adult psychotherapy, acute care of up to 10 h is reimbursed (as of October 20th 2020) with 120 €. Initial treatment of a maximum of 20 h is reimbursed at 115 €. Further treatment is possible with up to 30 sessions (105 €). The first max. 16 psychotherapy sessions are defined as trial intervention of PSYCHOnlineTHERAPY. Thereby, the trial definition of 16 sessions follows both trial feasibility considerations as well as psychotherapy dose-response findings, with 4–24 sessions being reported as optimal dose in routine treatment settings (44). Patients of all three trial arms will receive standard PNP-based psychotherapy following the first 16 sessions in case of still existing need of psychotherapy as defined by the therapist. As only psychotherapists with a CBT background are eligible for this trial, PNP-based psychotherapy will be CBT-based.

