Patient satisfaction will be assessed with a German short version [ZUF-8; eight items, score range: 8–32; (60)] of the Client Satisfaction Questionnaire [CSQ; (61)]. Higher scores are indicative for higher satisfaction. Internal consistency of the ZUF-8 is reported with a Cronbach's Alpha of 0.90 (60). In addition, reasons for dissatisfaction with the intervention will be assessed with 9 self-developed items.

Working alliance will be assessed with the German version (62) of the Working Alliance Inventory [WAI-SR; 12 items, score range: 12–60; (63)]. It covers the three subscales (a) agreement on tasks (four items), (b) agreement on goals (four items), and (c) development of an affective bond (four items). For the German Version, internal consistencies between α = 0.81 and α = 0.91 were reported for the subscales and internal consistencies between α = 0.90 and α = 0.93 for the total score (62, 64). Participants will complete the WAI-SR at T1 and at T3. Therapists only at T3. This will allow for a comparison between patients' and therapists' view on working alliance.

Psychotherapy adherence will be assessed by means of the number of completed online- and standard sessions. Per-protocol (PP) adherence is operationalized by the percentage of participants that completed their psychotherapy as recommended by their therapist (therapist-rating). Reasons for dropout are assessed by six items at post-treatment (T3; patient-rating).

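### The per-protocol analyses are defined by data provision, in conflict with the protocol's own treatment-based definition, so they do not test sensitivity to non-delivery

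*Protocol article*

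**What the plan says.** Statistical Analyses, Clinical Analyses, sets the main population: "All statistical analyses will be performed based on intention-to-treat (ITT) principle". On missing outcomes it says that "analyses will be corrected for missing data by applying multiple imputation". The per-protocol analyses follow in one sentence: "Additional multiple PP analyses will be conducted including only patients that provided data". No session count, module use or adherence rating enters that sentence.

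Assessments, Secondary Outcomes, uses the same label for something else: "Per-protocol (PP) adherence is operationalized by the percentage of participants that completed their psychotherapy as recommended by their therapist (therapist-rating". The same paragraph shows that delivery is recorded: "Psychotherapy adherence will be assessed by means of the number of completed online- and standard sessions". The last paragraph of the Covariates section adds therapist documentation after every session.

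Two further statements bear on what counts as compliant. The Abstract describes the blended arms as "alternating with Online self-help sessions (fix: 8/8; flex: 0–16", so zero online sessions is allowed in flex. The Intervention section says "Patients of all three trial arms will receive standard PNP-based psychotherapy following the first 16 sessions", where the therapist sees a continuing need.

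**The concern.** The focal hypothesis is non-inferiority. If part of a blended arm in practice receives only what the control arm receives, the arms become more alike and the ITT difference can shrink towards zero, which is the direction that supports the claim. A per-protocol analysis is the usual companion to ITT for this reason, and the Abstract announces one.

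Selecting on data provision does not do that job. A fix-arm patient with no completed online module who answered the questionnaires is kept. A patient who followed the planned format but did not return the questionnaires is dropped. The contrast between the ITT result and this set therefore shows mainly whether imputation matters. A reader who sees the two agree could take it as reassurance about delivery that the analysis does not give.

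**Working it through.** **The two definitions side by side.**
- Clinical Analyses: a patient enters the per-protocol analyses if data were provided. Treatment received is irrelevant. The text does not say whether data are needed at T3 only or at all of T0 to T3.
- Secondary Outcomes: a patient is per-protocol adherent if therapy was completed as the therapist recommended. Data provision is irrelevant.

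The second is a descriptive secondary outcome, and the first does not refer to it. A patient can meet either one without the other.

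**Reproducing the design.** Inputs from Sample Size and Power Calculation: margin 0.24 SD, one-sided α = 0.025, power 0.80, ICC 0.01, cluster size 12, 300 patients per arm. A true difference of zero is assumed.
- Unclustered n per arm = 2 × ((1.960 + 0.842)/0.24)² = 272.5
- Design effect = 1 + (12 − 1) × 0.01 = 1.11
- Clustered n per arm = 272.5 × 1.11 = 302.5, so 303 against the stated 300
- SE at 300 per arm = √(2 × 1.11/300) = 0.0860
- Power = Φ(0.24/0.0860 − 1.96) = 79.7%, against the stated 80%

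The design reproduces, so the same SE is used below.

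**Dilution in a set that keeps undelivered patients.** Assumptions, none of them document figures: delivered blended therapy is worse by exactly 0.24 SD; a share q of the blended arm is undelivered and does as well as CBT_standard. The mean difference is then 0.24(1 − q), and

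P(declare non-inferiority) = Φ((0.24 − 0.24(1 − q))/SE − 1.96) = Φ(0.24q/SE − 1.96).

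**The same with data providers only.** Assume also that 20% of outcomes are missing independently of delivery: 240 per arm, mean cluster size 9.6, design effect 1 + 8.6 × 0.01 = 1.086, SE = √(2 × 1.086/240) = 0.0951.

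| Share undelivered, q | All patients, SE 0.0860 | Data providers only, SE 0.0951 |
|---|---|---|
| 0% | 2.5% | 2.5% |
| 20% | 8.0% | 7.3% |
| 30% | 13.1% | 11.4% |
| 50% | 28.6% | 24.2% |

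The slightly lower figures on the right come only from the larger SE; the diluted mean difference is the same.

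**What a delivered-only set costs.** Keeping 300(1 − q) patients in the blended arm and 300 controls, SE = √(DE_q/(300(1 − q)) + 1.11/300), with DE_q = 1 + (12(1 − q) − 1) × 0.01.
- q = 20%: SE = √(1.086/240 + 0.0037) = 0.0907; power at zero difference 75.4%
- q = 50%: SE = √(1.05/150 + 0.0037) = 0.1034; power 64.1%

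If delivery is unrelated to prognosis, false non-inferiority at the margin stays at 2.5%.

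**The case against.** **The protocol may intend more than it says.** The word "multiple" in the per-protocol sentence leaves room for further sets, and the two sections could be read jointly as therapist-rated adherence analysed on observed data. Detailed cut-offs also normally sit in an SAP. That excuses missing cut-offs, but the article does state an inclusion rule, and that rule contains no treatment condition and no link to the adherence definition.

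**Flex and later sessions.** A reader might infer that a flex patient with no online session, or a patient given standard sessions after the first 16, is wrongly kept. The documents do not support that. Zero online sessions is within the flex range in the Abstract, and continued standard therapy is provided for in all three arms in the Intervention section and Table 1. Both are compliant. Non-delivery of online modules is a clear deviation only in fix.

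**Direction and size of the bias.** A reader might infer that ITT and the per-protocol set must agree, or give identical error rates. That would need no missing outcomes, or missingness unrelated to delivery; patients who leave therapy may also stop answering. Nor is dilution towards zero assured. A fix patient who skips modules without replacement has at most eight standard sessions against up to 16 in control, so the difference could widen and count against non-inferiority. The calculation also uses the simple T3 comparison from the sample size section, whereas the planned test is a bootstrap interval for the time-by-group interactions.

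**Delivery will be visible anyway.** Session counts are reported as a secondary outcome. That shows how much was delivered, but not whether the conclusion holds among those who received it.

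These objections limit the claim; the conflict between the two definitions remains.

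**Conclusion.** The point holds in a limited form. The per-protocol analyses, as stated, are an observed-data set. They conflict with the treatment-based meaning of per-protocol given elsewhere in the same article, and they leave this non-inferiority trial without a per-protocol check on non-delivery.

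The size is illustrative. With a true deficit exactly at the margin, undelivered patients equal to CBT_standard, and missingness unrelated to delivery, a data-providers-only set removes almost none of the dilution. The non-delivery shares and the 20% missingness are assumed, so the figures show what could happen, not what is expected.

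A reader might go further and require ITT and per-protocol to agree before non-inferiority is claimed. The documents describe a pragmatic trial analysed by ITT, and nothing in them requires that gate; it would be a sponsor's choice with a cost in power. The same holds for extra baseline adjustment: T0 is already an outcome occasion in the planned model.

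**What to change.** 1. Rename the analysis now described under Clinical Analyses as observed-data or complete-case, and state which time points must be present.
2. Reconcile it with Secondary Outcomes by defining a per-protocol set before outcomes are examined by arm, using the therapist rating of completion and the recorded session counts, arm by arm:
   - fix: online and standard sessions both delivered in the planned alternating format;
   - CBT_standard: no study module used;
   - flex: therapy completed as recommended, since zero online sessions is compliant.
3. If a flex analysis restricted to patients with at least one online session is wanted, report it only as a labelled sensitivity analysis.
4. Present the per-protocol result as a supportive consistency check beside ITT.

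The cost is wording, and no new data collection is needed. The downside is a smaller set selected after randomization, open to selection bias and with less power (75.4% at 20% non-delivery under the assumptions above), which is why it should support the ITT result and not replace it.
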